### Blinding

Research personnel responsible for survey administration and epidemiologic data analyses will be blinded to the timing of cluster transitions from control to intervention conditions. Because allocation is non-randomized and occurs at the cluster level, and only outcome assessors and analysts are blinded, formal unblinding procedures will not be required.

### Ethics Approval

This study has been reviewed and approved by the Institutional Review Board at the University of Chicago IRB24–1997, with reliance agreements established as needed for collaborating institutions. All study procedures will be conducted in accordance with applicable ethical guidelines and regulations.

### Risks and Protections

Risks associated with participation are expected to be minimal and may include potential discomfort discussing health-related topics or concerns related to sharing information on social media. Participants will be informed that they may skip questions or decline to participate in any study activity. The study team will take steps to minimize risks by emphasizing voluntary participation and protecting confidentiality.

### Oversight and Monitoring

Oversight of study conduct and participant safety will be guided by an Institutional Review Board–approved Data and Safety Monitoring Plan. Given the minimal-risk, educational nature of the intervention, a formal Data and Safety Monitoring Board will not be convened. Study oversight will be conducted by the Principal Investigator and research team in accordance with institutional and federal requirements.

If an adverse event occurs, the PI will report it promptly to the IRB, institutional compliance offices, and NIH in accordance with federal and institutional requirements. The study team will assess the event to determine its cause and evaluate whether it is related to study activities. When appropriate, the informed consent document and/or study protocol will be revised to incorporate additional safeguards identified through review of the event.

### Confidentiality and Data Security

All study data will be handled in accordance with applicable federal, state, and institutional regulations to ensure participant confidentiality. Prior to participation, promotores will receive an overview of study data collection procedures, including the use of REDCap-based questionnaires, social media engagement metrics, and publicly available epidemiologic data sources.

Each participant will be assigned a unique study identifier. Any files linking personal identifiers to study data will be accessible only to authorized research staff and will be stored separately from analytic datasets. These linking files will be destroyed following completion of data collection and prior to analysis. Identifiers and contact information will not be shared outside the research team.

Survey and social media analytics data will be collected and stored using secure, password-protected systems, including REDCap hosted at the University of Iowa. Qualitative data, including focus group recordings, transcripts, and coding files, will be stored on secure, password-protected institutional systems. Audio, video, and written materials will be assigned unique identifiers and de-identified prior to analysis. Recordings and transcripts will be encrypted, and access will be restricted to authorized study personnel.

Social media data shared by promotores will be limited to content and engagement metrics relevant to study objectives. Any data obtained from social media platforms will be handled in a manner that protects the privacy of both promotores and members of their networks.

De-identified vaccination coverage and healthcare utilization data will be obtained from the Chicago Data Portal and the Illinois Department of Public Health under applicable data use agreements.[34, 39] These data will be stored securely and linked to study datasets using geographic identifiers when permitted. Limited datasets (e.g., dates and zip codes) may be retained for future secondary analyses in accordance with institutional policies.

All publications and presentations will report only de-identified, aggregate data, and no identifying information will be included.

### Dissemination

Findings from this study will be disseminated through peer-reviewed publications and conference presentations. In addition, results will be shared with participating community-based organizations and promotores in accessible formats, including summaries and presentations tailored for community audiences. These dissemination efforts are intended to support ongoing health communication efforts and inform future interventions within Spanish-speaking communities.

In accordance with institutional policies and data use agreements, participant-level data will not be shared publicly to protect confidentiality. Statistical code may be made available upon reasonable request and subject to institutional review.

### Trial Status

At the time of manuscript submission, recruitment has begun and is ongoing, but data collection has not yet been completed. This study is registered on ClinicalTrials.gov (NCT06417762). This manuscript reflects protocol version 3.

## Discussion

This study will evaluate a community-engaged social media intervention designed to support promotores de salud in disseminating evidence-based health information within Spanish-language networks. Building on prior research demonstrating the influence of message characteristics and trusted messengers on health communication, this study aims to address gaps in understanding how health information circulates within these networks and which communication strategies are most effective in promoting engagement and informed decision-making. By integrating training in science communication with real-world application in social media environments, this study will generate evidence on both communication processes and intervention effectiveness.

Several features of the study design strengthen its ability to evaluate communication strategies within real-world settings. The stepped-wedge design allows for evaluation of intervention effects while ensuring that all participating communities receive the intervention over time. The use of promotores further leverages trusted community-based relationships to support message dissemination. The integration of multiple data sources, including surveys, qualitative data, social media analytics, and area-level health data, enables a more comprehensive understanding of both communication dynamics and downstream outcomes than would be possible using a single method alone. Evaluating communication strategies within real-world social media environments also enhances the relevance and potential scalability of the findings.

At the same time, several challenges should be considered in interpreting the results. The non-randomized design may introduce potential confounders, although analytic approaches will account for clustering and time effects. Reliance on self-reported data may introduce reporting bias, and variation in social media platform use and engagement across participants may result in heterogeneous exposure to intervention content. In addition, the study is conducted within a single metropolitan area, which may limit generalizability to other settings. Measurement of community-level outcomes may also be constrained by the availability and granularity of publicly available data.

Despite these considerations, findings from this study will provide important insights into how health information is shared, interpreted, and acted upon within Spanish-language social media networks. By identifying communication approaches that are both acceptable to community health workers and effective in engaging their networks, this work may inform the design of future interventions aimed at improving access to reliable health information and supporting informed decision-making in diverse communities. The integration of community-based expertise with digital communication strategies offers a potentially scalable model for addressing similar challenges in other settings.

## Figures and Tables

**Figure 1 F1:**
[figure not shown]
Geographically distinct community areas used for the recruitment of promotores.

**Table 1 T1:** Dime La VerDAD curriculum structure.

Session	Topic	Details	Homework
Focus Group	Baseline Discussion	Structured discussion to understand current social media practices, commonly encountered health claims, and communication experiences	
1	Designing Infographics	Introduction to infographics and visual communication principles; overview of Canva tools	• Join the study communication group (on WhatsApp) • Friend/follow *Dime La VerDAD* on social media platforms • Access the Canva folder • Share 2–3 practice posts on social media
2	Understanding Inaccurate Health Claims	Overview of different types of inaccurate health information and how it circulates online; discussion of potential impacts	• Invite approximately 45 social media network members to complete the pre-survey • Identify one vaccine-related health claim to address ○ Locate 2–3 credible sources • Begin drafting an infographic in Canva
3	Communicating Across Audiences	Principles of effective communication and audience engagement	• Develop draft infographics (1 Facebook, 1 Instagram) ○ Include a link to a credible resource • Draft a caption incorporating a personal narrative ○ Include (2–3) relevant hashtags and tags as appropriate
4	Evaluating Source Credibility	Methods for assessing the reliability of online sources (e.g., SIFT method, fact-checking tools)	• Verify sources using structured evaluation methods ○ Identify additional credible resources if needed • Revise draft infographic and caption based on instructor and cohort participant feedback
5	Applying Science Communication Strategies	Strategies for making evidence-based messages engaging and understandable	• Refine your infographic and caption based on feedback • Post standardized informational content provided by the study team
6	Responding to Disagreement on Social Media	Approaches to addressing dissent constructively and maintaining professionalism online	• Develop a strategy to address responses from people with opposing views • Present final infographic and communication strategy • Post standardized informational content provided by the study team • Post your finalized infographic and caption • Six months after baseline focus group, invite social media network members to complete the post-survey

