However, the effects of health information on social media may not occur uniformly across populations. Differences in social networks, access to information, and trusted sources can shape how health information is accessed, interpreted, and shared across communities [10–12]. These considerations are particularly relevant for Spanish-speaking communities, where the pathways through which health information circulates, the sources perceived as credible, and the reception of health information have not been well characterized [13–15]. For example, studies have shown that Spanish-speaking individuals may face challenges accessing trusted health information and often rely more heavily on social media and interpersonal networks for health-related content [16]. Levels of trust in health information sources also vary substantially within Spanish-speaking communities, further shaping how health messages are received and acted upon [17]. Understanding these differences is essential for interpreting how health information circulates within and across social media networks [18, 19].

In this context, understanding which characteristics of health messages influence how information is interpreted and shared on social media is also critical. Prior research suggests that message format plays an important role in shaping engagement and comprehension, with health messages that incorporate personal narratives often perceived as more relatable and easier to understand [20]. In addition to message characteristics, the credibility of the information source influences how messages are received and acted upon. Information delivered by trusted community communicators can shape attitudes and information-sharing behaviors, particularly when messages are conveyed by individuals with established relationships within their communities [21]. For example, collaborative efforts between healthcare professionals and community-based communicators have demonstrated the feasibility of producing culturally and linguistically appropriate health content for Spanish-speaking communities [22–24]. Similarly, in Illinois, promotores de salud (community health workers) have played an important role in disseminating health information within Spanish-speaking communities, including during the COVID-19 pandemic.[25][21] These findings highlight the importance of both message characteristics and source credibility in shaping how health information is understood and shared.

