Despite this work, there remains a limited understanding of how health information circulates and is interpreted within Spanish-language social media networks. In particular, few studies have examined how inaccurate or misleading health information is encountered in these settings or how responses grounded in scientific evidence are received by community members. In addition, it remains unclear which communication approaches are most effective in promoting engagement, recall, and informed decision-making in real-world social media environments. Addressing these gaps is essential for developing effective and scalable approaches to communicating evidence-based health information within Spanish-speaking communities.

To address these gaps, we developed Dime La VerDAD (“Tell Me the Truth”: Verify, Debunk, and Disseminate), a structured, community-engaged social media training program designed to support promotores de salud in disseminating reliable, evidence-based information about respiratory virus prevention. The program is grounded in principles of health communication and is designed to build practical skills in identifying inaccurate health claims, developing clear and accessible messages, and engaging effectively with social media audiences.

This study will evaluate the implementation and effectiveness of the Dime La VerDAD program using a stepped-wedge design across community-based cohorts. Specifically, it will characterize how health information is shared and interpreted within Spanish-language social media networks, evaluate whether a structured, evidence-based communication training program improves the quality and reach of health messaging, and assess whether narrative-based approaches differ from standard informational content in influencing engagement and vaccination-related decision-making. We hypothesize that promotores will be perceived as trusted messengers and that narrative-based posts will result in greater engagement and improved decision-making in favor of recommended immunizations.

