### Social Media Engagement

Social media engagement will be quantified using platform-derived metrics, including impressions, likes, comments, and shares. Count-based outcomes will be analyzed using Poisson or negative binomial regression models, as appropriate based on dispersion characteristics. Continuous or ordinal survey outcomes will be analyzed using linear or cumulative link mixed models, depending on distributional assumptions. Repeated measures of generalized linear mixed models will be used to assess changes in engagement over time while accounting for clustering within promotores and neighborhood clusters under the stepped-wedge design.

Characteristics of social media posts and audience responses will be extracted using large-language models and multimodal analytic approaches applied to text, images, and video content. These characteristics will include sentiment, discussion of personal experience, presence of scientific evidence, and patterns of agreement or disagreement. These features will be incorporated as independent variables in regression and machine learning–based predictive models to examine their association with engagement outcomes and to identify characteristics of posts associated with higher levels of interaction within promotores’ social networks.

In addition to quantifying the volume of engagement, analyses will examine the nature of engagement by evaluating the content of audience responses to promotores’ posts. These analyses will provide insight into how different types of communication strategies influence both the extent and quality of interaction.

Implementation fidelity will be assessed by quantifying the number and characteristics of posts produced, including adherence to training principles such as inclusion of credible sources and use of narrative elements.

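### Among the posts the curriculum assigns, narrative coincides with who made the content, and the listed engagement features omit authorship, so the narrative estimate would absorb some or all of any authorship effect

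*Protocol article*

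**What the plan says.** The last paragraph of the Background states the aim to "assess whether narrative-based approaches differ from standard informational content in influencing engagement and vaccination-related decision-making", and the hypothesis that "narrative-based posts will result in greater engagement and improved decision-making in favor of recommended immunizations". This point concerns the engagement half of that aim.

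Table 1 fixes what promotores are asked to post:

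- **Informational content.** The homework for Sessions 5 and 6 is "Post standardized informational content provided by the study team".
- **Narrative content.** The promotor picks a vaccine-related claim (Session 2), drafts infographics and is told to "Draft a caption incorporating a personal narrative" (Session 3). The next steps are "Revise draft infographic and caption based on instructor and cohort participant feedback" (Session 4), a further round of refinement (Session 5), and "Post your finalized infographic and caption" (Session 6).

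Under Data Analysis, Social Media Engagement, features extracted from posts and audience responses become independent variables in models of engagement: "These characteristics will include sentiment, discussion of personal experience, presence of scientific evidence, and patterns of agreement or disagreement". The list does not include whether the study team or the promotor made the content.

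**The concern.** The stated contrast is about message form: narrative or not. The assigned posts differ in form, but also in who made the content, who chose the topic, and how far it was tailored and revised. A promotor's followers may respond more to something the promotor made than to a supplied graphic, whether or not it tells a story.

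If so, the model attributes that response to the only listed feature that separates the two kinds of post, personal experience. The trial could then report that narrative raises engagement, and recommend teaching narrative, on the strength of a comparison between self-made and supplied material.

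**Working it through.** The plan gives no sample size, effect size or power for this comparison, so there is no figure to reproduce. The check has two parts.

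**1. Can narrative and authorship be separated?** Code each post type as (intercept, narrative, promotor-authored), taking the supplied informational content to be non-narrative:

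- supplied informational post: (1, 0, 0)
- finalized own infographic with narrative caption: (1, 1, 1)

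These two rows have rank 2 against three columns. With assigned campaign posts only, no covariate adjustment separates the two effects. Adding a third type, a promotor-authored post without narrative, (1, 0, 1), raises the rank to 3. The narrative effect can then be estimated, provided authorship is in the model.

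**2. How large is the bias if authorship is left out?** Let A be the rate ratio for promotor-authored versus supplied content, and q the share of non-narrative posts that are promotor-authored. Neither is in the document; both are assumptions. Set the true narrative ratio to 1 and let all narrative posts be promotor-authored. With mean rate m for supplied content:

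- expected rate, narrative posts: m × A
- expected rate, non-narrative posts: m × (1 − q) + m × q × A
- apparent narrative ratio: A / (1 − q + qA)

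For A = 1.5:

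- q = 0 (assigned posts only): 1.5 / 1 = 1.50
- q = 0.25: 1.5 / (0.75 + 0.375) = 1.33
- q = 0.5: 1.5 / (0.5 + 0.75) = 1.20

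Over a range of A:

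| Assumed A | q = 0 | q = 0.25 | q = 0.5 |
|---|---|---|---|
| 1.2 | 1.20 | 1.14 | 1.09 |
| 1.5 | 1.50 | 1.33 | 1.20 |
| 2.0 | 2.00 | 1.60 | 1.33 |

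The true value in every cell is 1.00. The bias shrinks as more self-authored non-narrative posts enter, but remains while authorship is omitted. If A = 1 there is no authorship bias.

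**The case against.** **The comparator is inferred.** The article never says that the supplied posts are the comparator, or that engagement will be tested by setting the finalized infographic against them. This stands. The inference rests on the near-identical terms in the Background and Table 1, and on the absence of any other described informational content.

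**Other posts may be analysed.** A reader might infer that narrative and authorship are inseparable throughout the engagement analysis. The document does not support that. Study Design describes a control phase of usual posting, Session 1 asks for practice posts, Participants describes monthly payment for campaign posting, and the data export described under Outcomes is not limited to assigned posts. These could supply self-authored posts with and without narrative. The complete overlap therefore holds for assigned posts only.

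**False-positive rates.** A reader might go on to calculate how often narrative would wrongly be declared superior. That needs the number of posts of each kind per promotor, their mean and dispersion, and a decision rule. The article gives none of these. It describes count regression and feature associations, not a paired test, so no such rate can be attributed to the plan.

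**The Background on source.** The sentence "These findings highlight the importance of both message characteristics and source credibility in shaping how health information is understood and shared" might be read as the protocol itself naming authorship as a separate driver. In context, source means the messenger, and both kinds of post reach the same network from the same promotor. The point does not rest on that sentence.

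**Detail left to a fuller document.** The feature list covers what is extracted from content, and a full covariate list may exist elsewhere. That has some force for the missing covariate. It does not change the homework in Table 1, which is fixed here and determines what the assigned posts can show.

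**Conclusion.** The point holds in a limited form. Among assigned posts, narrative is aliased with content authorship, topic choice and tailoring. If further promotor posts are modelled, the aliasing is partial, but with the features as listed the narrative coefficient would still absorb part of any authorship effect.

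The size is unknown. With no true narrative effect and an assumed authorship ratio of 1.5, the apparent narrative ratio runs from 1.5 (assigned posts only) to 1.2 (half of the non-narrative posts self-authored). Both the authorship ratio and that share are assumptions.

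A reader might infer that the trial's main result is compromised. It is not: the primary survey outcome, its sample size and the control-versus-intervention contrast do not depend on this comparison. What is affected is a stated secondary aim with a directional hypothesis.

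**What to change.** (a) Under Data Analysis, Social Media Engagement, add an indicator for study-supplied versus promotor-authored content to the engagement models. Estimate the narrative effect among promotor-authored posts: campaign, practice and usual posts, with and without personal experience. The study team knows which content it supplied, so the indicator needs no new data collection.

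(b) Describe any comparison of the finalized infographic with the supplied posts as a promotor-authored narrative package versus study-supplied content, not as the effect of narrative.

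The cost is precision and scope: the narrative estimate uses fewer posts, and the conclusion is narrower. The estimate also stays observational. Practice posts and control-phase posts precede most or all of the training, so timing relative to training needs to be in the model too.

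Randomizing a narrative caption onto one of the supplied posts is optional and not required. It would change the curriculum of a trial already recruiting. Unless the study team also writes the narrative caption, or the promotor writes both captions, it leaves caption authorship confounded with narrative.
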